#### Statistical analysis plan

A biostatistician will compare the mean number of ADR per patient at the center level by using Student’s *t* test or Wilcoxon’s rank test, as appropriate, with the number of enrolled patients in each center as a weighting factor. In addition, the biostatistician will generate hierarchical models (level 1: centers; level 2: physicians nested within centers; level 3: individuals nested within physicians) with an analysis at the level of the patient taking into account the intra-cluster correlations at different levels using a generalized linear model. This analysis will have the advantage of controlling for potential confounders at the individual and physician level. The results will be reported using the Consolidated Standards of Reporting Trials (CONSORT) criteria (see Additional file 1).

We further plan to communicate these results to pharmacologist and neurologist review and to congress.

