**Fig. 1 Fig1:**
[figure not shown]
Enrollment, interventions and assessments in the Vigip-SEP study

Centers will be stratified based on structure type then randomly allocated (1:1) to the experimental arm (these centers will introduce all patients to use of the App) or to the control arm (these centers will not introduce patients to use of the App). Centers will be informed of the randomization the day of the trial initiation visit.

Clustering avoids a “contamination” bias (in the epidemiological sense) of different patients followed by the same prescriber.

Neurologists will successively include all patients meeting the criteria until they have reached the number of subjects to be included. In 1 year, MS academic expert centers are expected to include 10 patients, and general hospitals and private practice neurologists are expected to include 5 patients. Neurologists will inform patients about the Vigip-SEP study and obtain the patients’ written informed consent.

CHU de Caen conforms to National Informatic and Liberty French Law and, therefore, patient confidentiality will be protected.

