### Outcome measurements

#### Primary outcomes

The primary outcome is the number of ADR patient reports. ADR reports will be collected in both arms for 6 months after the inclusion of each patient from the national database of French authority, ANSM (see “Data collection procedure” below).

An example of the method of aggregation is as follows. For center 1, *m*1 = *n*1 reports/*N*1 patients, where *n*1 is the number of ADR in the center, and *N*1 is the number of patients included in the center.

The method of aggregation in each group follows the formula Ʃ*mx*/*N*, where *N* is the number of centers in the group.

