#### Hypothesis

In the academic literature, no study has measured the impact of an App on increasing reports of ADR by patients. MedWatcher® is a user-friendly reporting App used to prepare and submit an adverse event report to the Food and Drug Administration for a hysteroscopic sterilization device. In 2012, a patient social media community adopted MedWatcher® to declare adverse reactions related to the device. On average, there were 15 times more reports via the App than via the traditional pharmacovigilance portal [19]. We assume that patient reporting will increase by 10-fold with the use of the mobile application My e-Report® over the traditional reporting method.

To follow the cluster-randomized design, the statistical unit will be the center. Therefore, the average number of ADR patient reports per patient will be pooled by center, and the comparison will be performed at the cluster (center) level. Estimation of number of centers required: this is a comparison of two means with an average for the arm standard of 20/3000 = 0.0067 or 6.7 per 1000 patients; and for the interventional arm of 200/3000 = 0.067 or 67 per 1000 patients. The power is 90% according to a bilateral test with 5% error risk and an estimated standard deviation of 0.04. Therefore, 10 centers in each arm are needed to test our hypothesis.

We will target to include 12 centers per arm to counter the trend in over-reporting due to informing physicians of the study (inflation factor). A total of 24 MS outpatient-clinic departments will recruit 180 patients (90 per arm) with the following distribution according to structure type: 10 patients per MS academic expert center, 5 patients per general hospital and 5 patients per private practice neurologist.

Statistical criteria for stopping the study: no intermediate analysis is planned, and the study will be stopped when all centers have obtained the required number of patients.

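### The primary outcome counts every centre equally but the primary test weights centres by enrolment, so the primary analysis is not fixed

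*Protocol article*

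**What the plan says.** All places are in the protocol article.

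- **Primary outcomes.** Each centre's value is its reports divided by its patients. "The method of aggregation in each group follows the formula" in which these centre values are summed and divided by the number of centres. Every centre counts the same.
- **Hypothesis.** The centre is the statistical unit and the sizing compares two means. "The power is 90% according to a bilateral test with 5% error risk and an estimated standard deviation of 0.04". The result is that "10 centers in each arm are needed to test our hypothesis"; 12 per arm are targeted. Academic centres are to recruit 10 patients each, general hospitals and private-practice neurologists 5 each.
- **Statistical analysis plan.** The centre means are compared by a t test or a Wilcoxon rank test, "with the number of enrolled patients in each center as a weighting factor". A generalised linear model is added with centres at the top, then "level 2: physicians nested within centers; level 3: individuals nested within physicians", to control for individual- and physician-level confounders.
- **Randomization** (text under Fig. 1). Centres are randomised 1:1 within structure type. The primary tests named are plain two-group tests, and structure type is not among the model's stated covariates.

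**The concern.** If all centres were the same size, the two weightings would agree. Here sizes differ twofold by design, and size follows structure type. Choosing a weighting therefore means choosing how much academic centres count against the others. If reporting differs by type, the two sections describe different target quantities. If it does not, they still give different estimates and p-values from the same data.

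The rank-test option adds to this: with the weight attached, it is not a procedure that can be run in standard form. An analyst following the text must either drop the weight or invent a method, and could do so after seeing the data.

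Two lesser matters follow. The test leaves out the factor on which centres were stratified. The supplementary model asks more of the data than the planned report count can give.

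**Working it through.** **1. The plan's own figure.** Inputs from Hypothesis: control mean 20/3000 = 0.0067, intervention mean 200/3000 = 0.067, SD 0.04, two-sided 5%, power 90%. Centres per arm = 2 × [0.04 × (1.960 + 1.282) / 0.060]² = 9.34, rounded up to 10. The stated figure reproduces, as an equal-weight, unstratified comparison.

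**2. What each centre counts for.** Per arm (Abstract and Hypothesis): 6 centres of 10 and 6 of 5, so 90 patients.
- Academic share: 6/12 = 50% with equal weights, 60/90 = 66.7% with patient weights.
- One report from a 5-patient centre adds (1/5)/12 = 1/60 with equal weights, and one from a 10-patient centre adds (1/10)/12 = 1/120. With patient weights each adds 1/90.
- Assumed example: rates of 0.10 in academic and 0.033 in other centres give an arm value of (0.10 + 0.033)/2 = 0.0665 or (2 × 0.10 + 0.033)/3 = 0.0777. With the rates reversed, the values are 0.0665 and 0.0553.

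**3. Precision.** The answer depends on the source of variation.
- Pure Poisson counts: the variance factor is (6/10 + 6/5)/144 = 0.0125 with equal weights and 1/90 = 0.0111 with patient weights. The ratio is 1.125, so equal weights have 12.5% more variance.
- Centre SD of 0.04 whatever the size, as in Hypothesis: patient weights reduce 12 centres to an effective 90²/(6 × 100 + 6 × 25) = 8100/750 = 10.8. Normal-approximation power, Φ(0.060/(0.04 × √(2/n)) − 1.960), falls from 95.7% to 93.6%.

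**4. Effect on the verdict.** Poisson counts were simulated for 12 centres per arm at the planned rates, with 3000 or more trials per scenario. The weighted and unweighted t tests reached different conclusions at 5% in about 10% of trials when types do not differ, with or without extra between-centre variation. They differed in 15-17% when academic centres report three times as often as the others, and in 11-16% under other assumed patterns.

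**5. Structure type.** Simulated power at the planned rates, with a Monte Carlo error of about 1 point. Compare across rows only, because the overall rate is scaled differently in each pattern.

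| Assumed rates, academic : general : private | Equal weights | Patient weights | Equal + type | Patient + type |
|---|---|---|---|---|
| 1 : 1 : 1 | 50% | 54% | 50% | 53% |
| 0.5 : 1 : 2 | 44% | 36% | 47% | 40% |
| 3 : 1 : 1 | 52% | 68% | 55% | 68% |

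Power is far below 90% because Poisson noise alone gives an intervention centre's mean an SD of √(0.067/10) = 0.082 or √(0.067/5) = 0.115, against the assumed 0.04. That is a separate matter.

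With equal rates of 0.067 in both arms and academic centres reporting three times as often, type I error was 3.0-3.4% for the unstratified equal-weight t test and 4.7-5.6% for the weighted one. For the weighted test with structure type it ranged from 1.5% to 7.6% over the scenarios run.

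With planned sizes and balanced arms, weights are constant within type. Adding structure type then changes the error term and not the estimate, so it does not settle the weighting conflict.

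**6. Supplementary model.** Expected reports are 90 × 0.00667 = 0.6 in control and 90 × 0.0667 = 6.0 in intervention, 6.6 in all. The chance of no control report is exp(−0.6) = 55%. In that case a log- or logit-link model has no finite maximum-likelihood arm effect.

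**The case against.** The strongest reply is that only part of this is an error. A condensed article may leave adjustment for strata to the full plan, and nothing printed excludes it. Leaving strata out does not bias the comparison; in the simulations it mostly made the test conservative. The gain from adding them depends on an assumed pattern. For the weighted test at planned rates it is nil when academic centres report more. A large gain (53% to 75%) appears only at rates of 0.1 against 0.3, far from the plan, with academic centres reporting least; reversing that order gives 80% to 85%. All of this stands, so structure type is put forward as a cheap improvement and not as a correction.

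A reader might also infer that patient weighting is the right choice because equal weighting loses 12.5% in variance. The documents do not support that: the figure needs pure Poisson noise, and under the plan's own constant SD the advantage reverses.

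Nor does the absence of a physician identifier from the article's data list show that none is collected, since such a list may be abridged. That a private-practice centre is a single neurologist is only suggested by its label. The model is supplementary, and its sparseness holds at the planned rates; at 0.1 against 0.3 an empty control arm is practically ruled out.

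None of this touches the conflict between the two weightings, which is in the printed text.

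**Conclusion.** The weighting conflict is an error as written. The outcome definition and the sizing use equal weights, the test uses enrolment weights, and one of the two tests offered cannot take weights in standard form. Academic centres move from 50% to 66.7% of the arm value. The significance verdict changes in about 10% of trials at the planned rates, and in about 10-17% if types differ. These proportions rest on planned centre sizes, Poisson counts and the assumed type patterns; the change in shares rests on the planned sizes alone.

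The documents do not show which weighting is better, that ignoring strata invalidates the test, or that the three-level model undermines the primary result. On the model, the fair statement is that about 6.6 reports cannot support two variance components plus confounders.

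**What to change.** 1. Before data are seen, choose one weighting and state it identically in Primary outcomes, Hypothesis and Statistical analysis plan. If patient weights are chosen, redo the sizing to match. If equal weights are chosen, delete the weighting clause.
2. Replace the weighted Wilcoxon option with a method that can be run: a re-randomisation test of the chosen estimate within structure type, or a van Elteren test if ranks are wanted. With 6, 3 and 3 centres per arm there are 924 × 20 × 20 = 369,600 balanced allocations, so the re-randomisation reference set is ample.
3. Include structure type in the primary centre-level analysis and take the p-value from the within-type re-randomisation, because the t reference is only approximate at this report count.
4. As advice: limit the patient-level model to arm, structure type and a centre effect, with penalised or exact estimation, and label it supportive.

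The cost is wording, since structure type is already collected. Adding it uses 2 degrees of freedom, about 2 points of power if types do not differ; the gain if they do runs from none to substantial.

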## Discussion

Application use by patients could be an integral part of the pharmacovigilance system that is in place in France. This study aims to improve the efficiency of the pharmacovigilance system by increasing the number of reports and, therefore, allowing earlier detection of events to prevent and minimize risks.

The robust methodology, with a clustered randomized national study, will determine the usefulness of national support for reporting by mobile application.

The results of this study should be available in the summer of 2018, and we hope that these results will be consistent with our assumption that (1) the efficiency of the post-marketing authorization system will be improved by an increase in reporting of ADR via the mobile application and (2) the therapeutic safety of MS patients will be improved by a better knowledge of the safety profile of DMD.

Developing a culture of reporting ADR by RR-MS patients is a relevant goal. In 2015, in France, 20 ADR were reported by MS patients compared with 271 ADR reported by physicians concerning first-line DMD according to data from the French National Database of Pharmacovigilance. In the future, we hope that this new method of reporting will improve pharmacovigilance by RR-MS patients and can be extended to include all new DMD. The overall goal is to be able to improve the early detection of unexpected adverse reactions not revealed by clinical consultations. If our hypothesis is confirmed, other neurological diseases could be explored using this method.

### Strengths and limitations

This study has several strengths. First, the design, a randomized control trial, will allow a causal interpretation in terms of outcomes. In addition, including several types of centers (academic expert centers, general hospitals and private practice neurologists) will increase the external validity of the results. Furthermore, the study is focused on the use of an innovative tool, a mobile application, by a population in real-life conditions.

We are also aware of several potential limitations. This is an open trial and, therefore, over-reporting due to informing the patients and physicians is expected and cannot be neutralized. Moreover, patients failing to report ADR by the App may have had a technical problem or may have forgotten to report the ADR. Indeed, the user-friendliness of the mobile application has not been tested. To counter this limitation, 1 month after inclusion, we will ensure by a telephone call that patients report all ADR and are able to use the mobile application effectively. Feedback from regional pharmacovigilance centers will also be investigated by a telephone call at 6 months after inclusion to explore patient satisfaction [16].

Currently, patients describe ADR via the App via free verbatim that is later coded by pharmacologists of pharmacovigilance centers using the MedDra dictionary. Encouraging this reporting requires the accompaniment of regional pharmacovigilance centers. In addition, informing patients, as proposed in the study, requires time by neurologists. Financial resources should be put in place for this support, which could be included, for example, in a patient education program.

Pharmacovigilance is a major public health issue. First-line DMD, whose risk profiles are not fully known, that have been newly released to the market must be carefully monitored. Patient involvement in the pharmacovigilance system is already accepted to be a valuable asset but must be further developed. RR-MS patients, who are already well-adapted to managing their disease, could be key players in effective pharmacovigilance. In a second phase, we plan to develop applications specifically dedicated to new DMD.

### Trial status

Recruitment has not been completed at the time of this submission.

## Abbreviations

ADR: Adverse drug reactions
App: Mobile application
DMD: Disease-modifying drugs
E2B: E2B does not have a direct translation to English. The International Conference on Harmonization of Technical Requirements for Registration of Pharmaceuticals for Human Use (ICH) published guidelines that designated “E” to stand for efficacy. E2B essentially defines what data elements need to be transmitted in individual case safety reports (ICSRs), regardless of the source or destination
EMA: European Medicines Agency
MS: Multiple sclerosis
RMP: Risk management plans
RR-MS: Relapsing-remitting multiple sclerosis
WHO: World Health Organization
